### Data Analysis

#### Subproject 1

For the claims data, control groups will be matched by age, gender, and time of diagnosis (year/quarter). We will analyze the utilization patterns longitudinally for the cohorts and will focus specifically on the health care service billing group. We will estimate the incidence of PCC diagnoses (*ICD* codes: U09.9, U07.4), as well as newly occurring comorbidities, which may also be in the context of PCC. Expected outcomes are: (1) SARS-CoV-2 related symptoms, (2) newly developed diseases (cardiovascular diseases, autoimmune diseases, mental health diseases). Here, a special focus will be on diseases related to PCC, irrespective of a specific PCC diagnosis (eg, ICD-10 codes: R53, G93.3, F06.7, R43, M79.1, I26, R05, F48.0, F41) [4,34]. Health care utilization is analyzed using a *State Sequence Analysis* (SSA) [35]. Analyses are conducted for the cohort of SARS-CoV-2 infections and the control groups. In the analysis, the health care utilization for primary and specialist care as well as their respective diagnoses will be analyzed in the time before and after the SARS-CoV-2 infection. A specific focus will be on the appearance of a PCC diagnosis or diagnoses of PCC-related conditions. SSA identifies individual care trajectories represented as ordered sequences of quarterly states, where each state reflects contacts with general practitioners, COVID-19 specialists, or other specialists. Dissimilarities between trajectories are quantified using a theory-driven cost matrix, and clusters of patients with similar utilization patterns are derived through an unsupervised medoid-based clustering procedure. The optimal number of clusters is selected based on established quality indices (eg, average silhouette width). Factors associated with the resulting care pathway clusters are subsequently analyzed using multivariable regression models.

Additionally, the potential health care utilization depends on regional factors. Therefore, the place of residence of the cohort is recorded at the level of the districts and independent cities of Bavaria as well as the degree of urbanization of the municipality of residence. The regional distributions of the cohort and utilization patterns are visualized and analyzed using *geographical information systems* (GIS). Differences are analyzed using hierarchical regression models.

#### Subproject 2

All audio recordings from the interviews will be transcribed verbatim to ensure an accurate representation of participants’ perspectives. The evaluation process of the qualitative interviews employs thematic content analysis, as outlined by Mayring, to identify patterns and themes that emerge from the narratives [33]. This analytical process will involve both deductive category application based on the interview guide and inductive category development derived from the data itself. To support transparency, traceability, and efficient data management, MAXQDA (version 24.9.1) software will be used for coding and category refinement. Throughout the analysis, regular team discussions will be conducted to enhance reflexivity and ensure the reliability and coherence of the coding framework.

Furthermore, the results of the quantitative and qualitative subprojects are compared, and aspects of care are identified where there are divergences between the qualitative experience and the quantitative analyses. The prepared results of the care pathways of the claims data analysis and the experiences of the interview study are presented to the participants of the focus group and discussed. In the focus group, recommendations for action will be developed. The transcript will be analyzed using qualitative content analysis following Mayring’s approach [33], which enables a systematic, rule-guided development of categories and the stepwise interpretation of the material.

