**Figure 1. F1:**
[figure not shown]
Mixed-methods study approach.

First, in a retrospective cohort study with claims data (Subproject 1) objective care pathways will be reconstructed based on routine data from the KVB. To do so, three cohorts will be defined, a cohort of patients with SARS-CoV-2 infection and a cohort of patients with other respiratory tract infection during the pandemic phase 2020 till 2022. To measure the impact that the pandemic had on the overall health care utilization, we will also form a historic control group with respiratory tract infections in the year 2019.

Second, a qualitative study (Subproject 2) will be conducted, including semistructured interviews with people affected by PCC concerning their individual subjective experiences and personal motivations for (non-) utilization of care.

The integration of the results will take place at the interpretation stage through systematic triangulation. Quantitatively identified care pathways will be compared with themes derived from patient interviews to identify areas of convergence, complementarity, and divergence. Joint displays will be developed that compare quantitative care trajectories with qualitative interview data, enabling structured comparisons across data sources. This will be achieved by using the software MAXQDA (version 24.9.1), as referenced by Kuckartz [27,28].

All results will be synthesized in a focus group in order to record and understand the care processes holistically and to classify them in the light of the existing evidence. The focus group will serve to validate and refine the results of the individual interviews, to contrast individual experiences within a group setting, and to enable in-depth exploration of shared experiences and interpretive patterns. Moreover, it supports the development of evidence-informed recommendations for care improvement. The synthesis will be published in scientific journals and made accessible to affected individuals and care providers to ensure broad dissemination and practical impact.

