### Participants and Data Collection

The subprojects will be informed by a systematic literature review performed before the project (manuscript forthcoming).

*Subproject 1:* KVB claims data will be used for the analysis. The KVB data includes all claims for ambulatory physicians in the State of Bavaria made by insured persons residing in Bavaria. The analysis is based on the *Bavarian COVID-19 Cohort* which was established from anonymized billing records of all patients with statutory health insurance in Bavaria. Both general practitioners and medical specialists submit details on patient encounters, including treatments, diagnoses, and billing information, to the KVB in each quarter. The dataset includes pseudonymized patient identifiers, demographic variables (age, sex, region), diagnoses (International Classification of Diseases, 10th Revision, ICD-10 codes with diagnostic certainty) and billed services (EBM codes, specialty, and practice identifiers). This structure allows longitudinal tracking of health care utilization, comorbidities, and treatment patterns across cohorts.

Out of 9,202,930 individuals with any respiratory infection, 4,247,455 had a confirmed COVID-19 diagnosis and the remained any other respiratory infection. For the analysis, three cohorts were randomly drawn:

COVID-19 (2020–2022): 196, 000 individuals with a confirmed diagnosis of COVID-19, ie, *ICD* codes U07.1 or U08.9 or U09.9 (secured and suspected diagnoses)Control (2020–2022): 140,000 individuals matched to the COVID-19 cohort by age and sex who received a confirmed ambulatory diagnosis of a respiratory infection (*ICD* J00*–J22*, J40*–J42*) in the same quarter.Historical control (2019): 140,000 individuals with a confirmed respiratory infection (*ICD* J00*–J22*, J40*–J42*) diagnosed in 2019, matched by age and sex to the COVID-19 cohort

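### The two accounts of how the 2019 control group is matched conflict: year matching is impossible for it, and its definition leaves index season uncontrolled

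*Protocol article*

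**What the plan says.** The protocol article describes the matching for Subproject 1 in two places.

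- **Participants and Data Collection** defines the cohorts. The COVID-19 cohort (2020–2022) has "196, 000 individuals with a confirmed diagnosis of COVID-19". The concurrent control group has "140,000 individuals matched to the COVID-19 cohort by age and sex who received a confirmed ambulatory diagnosis of a respiratory infection", with that diagnosis falling "in the same quarter". The historical group has "140,000 individuals with a confirmed respiratory infection", "diagnosed in 2019, matched by age and sex to the COVID-19 cohort".
- **Data Analysis, Subproject 1** states one rule for both: "control groups will be matched by age, gender, and time of diagnosis (year/quarter").

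Study Design gives the historical group its own purpose. To gauge how the pandemic changed overall utilization, "we will also form a historic control group with respiratory tract infections in the year 2019". Data Analysis then builds the utilization analysis on care states recorded quarter by quarter, before and after the infection.

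**The concern.** The rule in Data Analysis is written for control groups in the plural, and one of the two cannot satisfy it. The cohort definition for that group states a weaker rule without time of diagnosis. A reader cannot tell whether calendar quarter was used when the 2019 group was formed.

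This matters because the outcome is a sequence of quarterly states. The index quarter decides which seasons the first, second and later quarters of each sequence fall in. If the 2019 controls have a different mix of index quarters from the 2020–2022 cohorts, the same position in the sequence corresponds to different seasons in the two groups. Any seasonal variation in ambulatory contacts then enters the contrast and can be mistaken for a change brought about by the pandemic.

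**Working it through.** There is no sample-size or power figure to reproduce. The check compares the two sections and then asks what follows.

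**Step 1. The two rules side by side.**

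| Group | Participants and Data Collection | Data Analysis | Compatible? |
|---|---|---|---|
| Concurrent, 2020–2022, n = 140,000 | age, sex, same quarter | age, gender, year/quarter | Yes |
| Historical, 2019, n = 140,000 | age, sex | age, gender, year/quarter | No |

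**Step 2. What is possible for 2019.** The diagnosis years are {2019} for the historical group and {2020, 2021, 2022} for the cases. They have no year in common, so matching on year is impossible. The cases span 3 × 4 = 12 year-quarters and the historical group 4. Calendar quarters one to four occur in both periods, so matching on calendar quarter is possible.

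**Step 3. What follows if the cohort definition is taken literally.** Within an age-sex cell, let p_q be the share of COVID-19 cases with calendar index quarter q, and h_q the same share among the 2019 controls. Let u_q be the expected utilization at a given point in the sequence for someone indexed in quarter q, in the absence of any pandemic effect. The seasonal part of the contrast is

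bias = Σ_q (p_q − h_q) × u_q.

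It is zero if the quarter shares agree or if u_q does not vary with q. Matching on age and sex alone secures neither. The shares h_q then follow the respiratory infections of 2019, while p_q follows the COVID-19 diagnoses of 2020–2022. The document gives neither set of shares, nor u_q, so the bias cannot be computed. The same expression applies if the historical group is compared with the concurrent controls, because they are tied to the cases' quarters.

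**Step 4. What else the index quarter carries.** According to Results, the claims data cover 2019 to 2022. Assuming complete calendar years, a 2019 control has:

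| Index quarter 2019 | Earlier quarters in the data | Later quarters still in 2019 |
|---|---|---|
| 1 | 0 | 3 |
| 2 | 1 | 2 |
| 3 | 2 | 1 |
| 4 | 3 | 0 |

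The quarter mix therefore also decides how much pre-index history the group has, and how soon its follow-up enters the years that the article calls the pandemic phase. That is a further reason to state the mix.

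**Step 5. The cohort sizes.** 196,000 : 140,000 = 1.4 = 7 : 5 exactly, or 140,000 / 196,000 = 0.714 controls per case in each control group. Frequency matching at 5 controls per 7 cases yields these sizes with age, sex and quarter balanced. The sizes alone neither show nor exclude imbalance.

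**The case against.** The strongest defence is that this is loose wording. The slash in year/quarter may mean quarter where year cannot apply, and the 2019 controls may in fact have been matched on calendar quarter. An article condenses a fuller plan, and matching type and ratio are details commonly left to that plan. The plan also compares periods before and after infection and names regression models for pathway clusters and for regional differences, so the comparisons need not be unadjusted.

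Much of this stands. Calendar-quarter matching was possible and may have been done, so the seasonal mismatch is not established. The absence of a matching ratio or covariate list is no finding. But the defence does not remove the contradiction. The cohort definition names the quarter for the concurrent group and omits it for the historical one in the next item, which reads as a real difference between the two. Nor does a before-and-after comparison remove season by itself when the groups are indexed at different times of year.

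A reader might go further and infer from the sizes that 196,000 − 140,000 = 56,000 cases (28.6%) have no partner in each control group. That assumes one-to-one matching without replacement, which the article never states. Frequency matching at 7:5, or reuse of controls, would balance the matching factors at these sizes.

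**Conclusion.** The contradiction is real. Data Analysis states a matching rule that the 2019 group cannot meet as to year, and Participants and Data Collection gives that group a rule without any time element. If the latter describes what was done, season of index is uncontrolled in the historical contrast, which involves 140,000 historical controls. That number is the size of the group and not of a bias; the bias may be nil or material, and the document does not settle which.

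The conclusion rests on two assumptions: that the 2019 group was drawn without regard to quarter, as its definition reads, and that ambulatory utilization varies by season.

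Two wider readings are not supported. The concurrent comparison cannot be called unbalanced in time, because its controls are described as diagnosed in the same quarter as the cases. Nor should a seasonal difference in the historical contrast be described as one that will be taken for an effect of SARS-CoV-2. That group's stated purpose is to measure the impact of the pandemic on utilization, and that is the estimate at risk.

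**What to change.** 1. Reconcile the two sections: concurrent controls matched on age, sex and year/quarter of diagnosis; historical controls on age, sex and calendar quarter. If calendar quarter was not used when the 2019 group was drawn, say so.
2. Before any outcome comparison, tabulate age, sex and index quarter for the 196,000 cases and for each group of 140,000 controls.
3. In analysis, weight or standardize the historical controls to the COVID-19 cohort's age by sex by calendar-quarter distribution. Within an age-sex cell the weight is p_q / h_q; across cells it is the case share divided by the control share. This aligns season but does not supply the pre-index quarters missing for early-2019 index dates, so report the available window by index quarter.

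The cost is a wording change, a little analysis work and some precision. The effective number of historical controls becomes (Σw)² / Σw², which cannot be computed until the quarter shares are tabulated. No new data are needed: age, sex and diagnoses are in the dataset and claims are submitted by quarter. Results places the analyses up to April 2027. Neither restricting the cases to a subset nor changing the utilization model is needed for this point.

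### U07.4 counts as a PCC diagnosis but does not mark COVID-19 status, so a PCC case by the plan's own definition can be drawn as a pandemic-period control

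*Protocol article*

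**What the plan says.** Two places in the protocol article fix ICD code lists that bear on who has had COVID-19.

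- **Participants and Data Collection, Subproject 1 (COVID-19 cohort).** This cohort is "196, 000 individuals with a confirmed diagnosis of COVID-19", spelled out as "codes U07.1 or U08.9 or U09.9 (secured and suspected diagnoses"). The list is introduced by ie, so it reads as complete.
- **Same section (pandemic-period controls).** These are "140,000 individuals matched to the COVID-19 cohort by age and sex" and "who received a confirmed ambulatory diagnosis of a respiratory infection (*ICD* J00*–J22*, J40*–J42*) in the same quarter". No U code is named as an exclusion.
- **Same section (source population).** Of 9,202,930 people with any respiratory infection, "4,247,455 had a confirmed COVID-19 diagnosis and the remained any other respiratory infection".
- **Data Analysis, Subproject 1 (outcome).** The plan is to estimate the "incidence of PCC diagnoses (*ICD* codes: U09.9, U07.4"). The same paragraph makes the appearance of a PCC diagnosis, or of PCC-related conditions, a particular focus. It also says that the analyses cover both the SARS-CoV-2 cohort and the control groups.

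The Introduction defines PCC as a condition that follows a SARS-CoV-2 infection.

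**The concern.** By the article's own definition a PCC diagnosis implies an earlier SARS-CoV-2 infection. The plan treats its two PCC codes in opposite ways. U09.9 alone is enough to enter the COVID-19 cohort. U07.4 alone does not admit a patient, and it is not stated to keep a patient out of the controls. No reason is given for the difference.

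What is at stake is the purity of the comparator. The Discussion says that the study will judge service use against control cohorts. If some controls are PCC patients under the plan's own outcome definition, they bring PCC diagnoses, PCC-related diagnoses and PCC-type care sequences into the group meant to represent other respiratory infections. This moves the contrast toward no difference. A non-zero PCC frequency among controls could then also arise from the mismatch of code lists alone.

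**Working it through.** **Step 1: compare the code lists.**

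| Purpose | Codes | Section |
|---|---|---|
| Marks COVID-19 status | U07.1, U08.9, U09.9 | Participants and Data Collection |
| Counts as a PCC diagnosis | U09.9, U07.4 | Data Analysis |
| Admits a pandemic-period control | J00–J22, J40–J42 in the same quarter | Participants and Data Collection |

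PCC codes minus COVID-19 entry codes: {U09.9, U07.4} − {U07.1, U08.9, U09.9} = {U07.4}. One PCC code falls outside the entry list.

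**Step 2: who is affected.** All three conditions must hold: U07.4 is recorded; none of U07.1, U08.9 or U09.9 is recorded; and a qualifying J code is recorded in the matched quarter. A U07.4 patient who also has one of the three entry codes qualifies for the COVID-19 cohort and is outside this point.

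**Step 3: where such a patient sits.** The non-COVID part of the source population is 9,202,930 − 4,247,455 = 4,955,475. If the split uses the three entry codes, the patient in Step 2 falls in this remainder. Whether or not controls are drawn from the remainder, the stated control rule admits the patient.

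**Step 4: possible number among controls.** The article gives no count, so the share *c* of controls is an assumption, varied over a wide range. Number = *c* × 140,000.

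- *c* = 0.01%: 0.0001 × 140,000 = 14
- *c* = 0.1%: 0.001 × 140,000 = 140
- *c* = 1%: 0.01 × 140,000 = 1,400

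**Step 5: effect on the contrast.** Let *p* be the PCC incidence in the COVID-19 cohort, assumed to be 5%. With clean controls the difference is *p* − 0. With contaminated controls it is *p* − *c*. The relative loss is *c*/*p*.

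- *c* = 0.01%: 0.01/5 = 0.2%
- *c* = 0.1%: 0.1/5 = 2%
- *c* = 1%: 1/5 = 20%

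The same ratio applies to any outcome whose excess comes from PCC patients. If each such patient adds an excess *D*, the cohort mean rises by *pD* and the control mean by *cD*, so a fraction *c*/*p* of the difference is lost. This takes the excess to be equal in both groups.

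The article states no figure of its own on this point, so there is nothing to reproduce.

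**The case against.** **The group may be tiny.** Three conditions must coincide, and the article shows neither how often U07.4 was billed nor in which quarters. This stands. The size is unknown and may be negligible.

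**Some of the reasoning is inference.** The three codes are attached to the drawn cohort, not to the 4,247,455. The article does not say that controls come from the remainder. It also does not say outright that PCC incidence will be contrasted between groups: the sentence on analysing cohort and controls follows the one on state sequence analysis. Detailed control exclusions may be in a fuller document. All this is fair, and silence on exclusions would not be a point in itself. But the article does state both code lists, and they disagree about what U07.4 means.

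**A rule on U07.4 alone would be lopsided.** Read literally, the control rule bars no U code at all, so U07.1 or U09.9 among controls could matter more. This stands, and any correction has to treat all four codes alike.

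**The contamination would be visible.** If U07.4 is counted among controls, it will appear in the tables. That is partly true, but counting such patients does not take their care sequences out of the comparator.

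**Stronger readings that the article does not support.** A reader might infer that PCC incidence in the COVID-19 cohort is biased because patients with only U07.4 are absent from it. They are absent from numerator and denominator alike. With no recorded infection quarter they also have no usable index date for an analysis of care before and after infection. A reader might also take a loss of about a fifth as the expected effect; it is only the top of an assumed range.

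**Conclusion.** The two code lists conflict, and the conflict allows a patient who is a PCC case by the plan's own definition to serve as a pandemic-period control. The direction of the resulting bias is toward no difference.

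Its size cannot be derived from the article. With 0.01% to 1% of controls affected and a PCC incidence of 5% in the COVID-19 cohort, all of them assumptions, the loss runs from about 0.2% to 20% of the difference. The article does not show that any such control was actually drawn. The conclusion is therefore limited to possible contamination of the comparator, of unknown and perhaps small extent. It is worth correcting because the check is cheap and PCC diagnoses are a stated focus.

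**What to change.** 1. Use one harmonised set of SARS-CoV-2 and PCC codes: U07.1, U08.9, U09.9 and U07.4.
2. Exclude from the pandemic-period controls anyone with any of these codes at or before the index quarter.
3. Apply one rule to a first later occurrence in a control, the same for all four codes. Because censoring at that point conditions on an event after index, show results with and without it.
4. Report how many controls each step affects.
5. Do not give patients with only U07.4 the quarter of that code as their infection date. Report their number separately.

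**Cost.** The dataset already holds ICD-10 codes with diagnostic certainty, and the Results section has analyses running until April 2027, so this needs a code check and a small amount of extra analysis. Some controls are lost. For patients with only U07.4 this would be at most 1% of 140,000 at the top of the assumed range; screening on the other three codes may remove more, and the article gives no basis for estimating how many. If the count proves close to zero, one sentence reporting it settles the point.
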